#### Cognitive Flexibility Inventory

The Cognitive Flexibility Inventory (CFI) (43) is a 20-item self-report questionnaire that assesses three aspects of cognitive flexibility: tendency to perceive difficult situations as controllable, ability to perceive multiple alternative explanations for life occurrences and human behavior, and ability to generate multiple alternative solutions to difficult situations. The CFI has demonstrated good internal consistency (α = 0.79) and high test-retest reliability (43).

### Other Factors

#### Sociodemographic Questionnaire

Information pertaining to participant's age, ethnicity, marital status, parity, education level, income level, medical history, family psychiatric history, etc., will be collected.

### Cognitive Behavioral Therapy for Sexual Concerns During Perimenopause

Cognitive Behavioral Therapy for Sexual Concerns during Perimenopause (CBT-SC-Peri) will be offered in an individual format. It is a four-session protocol that takes place weekly for up to 90 min in duration. Sessions are administered by one of the study investigators or a trained Ph.D.-level graduate student therapist, supervised by the principal investigator (PI) who is a licensed clinical psychologist. Once participants have completed the four treatment sessions, a post-treatment assessment will be completed within 2-weeks, in which the battery of questionnaires will be re-administered. The content provided during each session includes evidence-based strategies designed to address sexual concerns during perimenopause and are provided in detail in Table 2. As this is an individual CBT protocol, content will be tailored to address the specific problems relevant for each participant. Session components include psychoeducation on sexual concerns during perimenopause, cognitive restructuring strategies, behavioral experiments, and therapeutic exposure. Participants are given materials including worksheets both from our published Cognitive Behavioral Workbook for Menopause (44), as well as worksheets that were developed specifically for this protocol.

**Table 2 T2:** CBT-SC-Peri Session-by-Session Content.

**Session 1**	- Introduction and psychoeducation on the menopausal transition in general (including physiological and hormonal changes and common symptoms associated with menopause). Information on the range of common sexual concerns that women experience throughout the transition (e.g., desire, satisfaction, pain, dryness) will be communicated. - Introduction to the CBT treatment model and role of thoughts and how they contribute to sexual concerns - Introduction to thought monitoring - Homework: reading material and worksheets to record practice
**Session 2**	- Check in and review of homework - Introduction to common cognitive distortions and unhelpful beliefs/expectations related to sexual concerns. Identification of participant's specific cognitive distortions. - Introduction to cognitive strategies for more helpful and balanced thinking (best friend and examine the evidence techniques) - Homework: assigned related reading material and worksheets to record practice with cognitive strategies
**Session 3**	- Check in and review of homework - Review of CBT modal and introduction to the role of problematic behaviors in sexual concerns (e.g., avoidance). - Introduction to behavioral experiments to challenge unhelpful beliefs and to promote more helpful and healthy behaviors to address sexual concerns - Homework: assigned related reading material and worksheets to record behavioral experiments and therapeutic exposures. Continued practice of cognitive strategies
**Session 4**	- Check in and review of homework - Continuation of behavioral experiments and previously learned strategies - Identifying longer-term goals and plan for maintaining gains

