#### Sample Size

Based on our data from our CBT for menopausal symptoms randomized controlled trial (19), as well as in previous studies (20) assessing the efficacy of CBT for sexual concerns in menopausal women, we estimate a medium effect size of 0.5 for our study. Using an ANCOVA power analysis to calculate sample size, and with a level of significance set at α = 0.05 and a study power set at 80%, 68 participants are required to conduct our study. Adjusting our sample for a 20% attrition rate, we plan on recruiting 82 participants.

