#### Study Design

This is an open waitlist study whereby eligible participants will be assigned to a treating clinician and will complete 4 weeks of the CBT-SC-Peri treatment protocol, followed by a post-treatment assessment. If a treating clinician is not immediately available, participants will be placed on that clinician's waitlist for 4 weeks. They will then be re-assessed after the 4-week waitlist period and then undergo the four-session treatment, followed by a post-treatment assessment. For a flowchart of trial procedures, see Figure 1.

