#### Telephone Screening and Study Visits

Women who are interested in participating will receive an initial telephone screen to ensure eligibility. Following informed consent, participants deemed eligible will be enrolled into the study and complete their baseline assessment consisting of a structured clinical interview (Mini International Neuropsychiatric Interview for DSM-5 and the Sexual Disorders Module of the Diagnostic and Research Tool for DSM-5) and self-report measures. Upon confirming eligibility at the baseline assessment, participants will be assigned to a treating clinician to undergo four weekly sessions (up to 90 min) of individual CBT-SC-Peri. If a treating clinician is not immediately available, participants will be placed on a waitlist for 4 weeks before starting treatment. Participants who are on the waitlist for treatment will be asked to complete the self-report measures following the waitlist period/before starting treatment. To reduce attrition, participants will be compensated with a $20 gift card following each assessment visit at baseline, post-waitlist (for those in the waitlist group), and post-treatment, in addition to travel reimbursement via the form of a parking pass or bus tickets (if an in-person visit is conducted).

Because of the short duration of the treatment and the sensitive nature of the topic (sexual concerns), there may be an unintended effect of the study namely, no improvement or worsening of symptoms. Should this occur, the research participant will be offered further care by our treatment team within the WHCC, a clinic that is equipped with a multidisciplinary team including psychiatrists, obstetricians-gynecologists, and psychologists.

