### Statistical Analysis Plan

Treatment response will be determined using multiple measures, as identified in the assessment battery, and distinguished between primary and secondary efficacy analyses. A series of repeated measures analysis of covariance (ANCOVA) will be used to examine condition differences. A two (treatment vs. wait-list) by two (time: pre-treatment, post-treatment) repeated measures ANCOVA will be used to examine differences in both primary and secondary outcomes, specifically sexual satisfaction and desire, body image, partner satisfaction, vasomotor symptoms, as well as depression and anxiety symptoms. Covariates for all analyses will include age, current marital status, medication use at baseline, treatment delivery method, and baseline depression and anxiety severity. If continuous variables do not meet the assumptions of normality, as assessed by the Shapiro-Wilk test, we will use non-parametric methods, with alpha levels set at 0.05.

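### The treated group's outcome assessment is triggered by completing all four sessions, while the wait-list reassessment follows a nominal 4-week wait, so outcome collection depends on adherence in one group only and runs on a different clock in each

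*Protocol article*

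**What the plan says.** The section describing the intervention sets the treated group's follow-up: "Once participants have completed the four treatment sessions, a post-treatment assessment will be completed within 2-weeks". The same section gives the schedule: "It is a four-session protocol that takes place weekly for up to 90 min in duration". Study Design describes the period slightly differently; there, participants "will complete 4 weeks of the CBT-SC-Peri treatment protocol, followed by a post-treatment assessment".

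For women who wait, Study Design says "They will then be re-assessed after the 4-week waitlist period". Telephone Screening and Study Visits adds that they "will be asked to complete the self-report measures following the waitlist period/before starting treatment". Neither place gives a window in days, and neither makes this assessment depend on attending anything.

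The Statistical Analysis Plan section states: "A series of repeated measures analysis of covariance (ANCOVA) will be used to examine condition differences". It specifies two conditions (treatment, wait-list) by two times (before, after). The listed covariates are age, marital status, baseline medication use, delivery method, and baseline depression and anxiety. Time since baseline is not among them. Sample Size plans for losses: "Adjusting our sample for a 20% attrition rate", giving 82 recruits. Table 1 has one post-treatment column per group and no column for women who discontinue.

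**The concern.** The two follow-up measurements that form the comparison are reached by different routes. In the treated group the trigger is finishing session 4. In the wait-list group it is the end of a waiting period. A treated woman who stops after session 1, 2 or 3 never meets the condition that triggers her assessment. A wait-listed woman who would have stopped had she been treated is still due for hers.

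This matters because stopping is probably related to outcome. Telephone Screening and Study Visits itself foresees that some women may not improve or may get worse, given the short treatment and sensitive topic. If such women are over-represented among early stoppers, the treated mean is taken from a favourably selected subset. Conditions are also assigned by clinician availability, not by randomisation, so the comparison has little protection against further selection after entry.

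The timing question is secondary. The treated assessment is counted from the last session and the wait-list assessment from the start of the wait. Nothing in the article makes the two intervals equal.

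**Working it through.** **1. Inputs**

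- Four weekly sessions, so session 4 falls 3 weeks after session 1 (intervention section).
- Alternatively, four full weeks of treatment before assessment (Study Design).
- Treated assessment 0 to 2 weeks after the sessions end (intervention section).
- Wait-list assessment at nominally 4 weeks (Study Design; Telephone Screening and Study Visits).
- Effect size 0.5 and attrition 20% (Sample Size).
- The gap from baseline to session 1, the split of attrition by group, and the benefit to early stoppers are not given. They are assumptions below.

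**2. The plan's own attrition figure**

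68 × 1.2 = 81.6, rounded to 82, reproduces the recruitment target from the stated 68. The allowance applies to the whole sample: 82 × 0.8 = 65.6, so about 65 women with a follow-up value. It does not say how many losses fall in each group. This point rests on no sample-size figure, so no new sample size follows from it.

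**3. Elapsed time**

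Let g be the gap in weeks from baseline to session 1, and take the wait to start at baseline.

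| Reading | Treated assessment | g = 0 | g from 0 to 2 (assumed) | Difference from week 4 at g = 0 |
|---|---|---|---|---|
| Session 4 at week 3 | g + 3 to g + 5 | weeks 3–5 | weeks 3–7 | −1 to +1 |
| Four weeks in full | g + 4 to g + 6 | weeks 4–6 | weeks 4–8 | 0 to +2 |

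The two readings are alternatives and should not be joined into one range. On either, the intervals can coincide. With no start gap they differ by at most 1 week on the first reading and at most 2 weeks on the second.

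**4. Effect of assessing completers only (illustrative)**

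Let p be the share of treated women who stop early, c the completers' gain over wait-list and s the stoppers' gain. The effect in all treated women is (1 − p) × c + p × s. An estimate from completers alone is c. Take c = 0.5 SD, and assume the wait-list mean is not distorted by its own losses.

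| p | s = 0: all treated | c ÷ all treated | s = 0.25: all treated | c ÷ all treated |
|---|---|---|---|---|
| 10% | 0.9 × 0.5 = 0.450 | 1.11 | 0.450 + 0.1 × 0.25 = 0.475 | 1.05 |
| 20% | 0.8 × 0.5 = 0.400 | 1.25 | 0.400 + 0.2 × 0.25 = 0.450 | 1.11 |
| 30% | 0.7 × 0.5 = 0.350 | 1.43 | 0.350 + 0.3 × 0.25 = 0.425 | 1.18 |

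If stoppers gain as much as completers (s = 0.5), there is no distortion. If women stop because they already feel better (s above 0.5), the direction reverses.

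**The case against.** The strongest reply is that a journal article condenses the full protocol. Handling of early stoppers, the analysis set and the missing-data method usually sit in documents that are not shown, and the intervention section may only describe ordinary visit timing. This stands for the analysis set and the missing-data method, whose absence is no finding. It does not dispose of the assessment trigger, which the article states. No later analysis plan can recover questionnaires that were not collected. With only two time points, a treated woman without a follow-up value contributes a baseline alone, and any imputation would have to borrow from women who finished.

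Several stronger readings are tempting and go beyond the text:

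- A reader might infer that completers are compared with all controls, or that losses are excluded from one group only. The article defines no analysis set. Its 20% allowance covers the whole sample, its gift cards at the post-waitlist visit show that losses are expected there too, and a repeated measures ANCOVA in its usual form needs both values in both groups.
- A reader might infer that controls are measured at exactly 4 weeks. No window is stated for them, so the time is nominal.
- A reader might take 25% or 11% as the bias of this trial. Those figures follow wholly from the assumed stopping rate and stopper benefit. Nothing in the article shows that early stoppers are the non-responders.
- A reader might add days since baseline as a covariate. That time is partly determined by condition, so adjusting for it is questionable, and it is largely redundant once the windows match.

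It is also fair that a difference of a week or two may matter little. The documents give no rate of spontaneous change from which to estimate its effect.

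**Conclusion.** The concern holds in a limited form. As written, outcome collection depends on treatment adherence in the treated group and on elapsed time in the wait-list group, and the two clocks start from different events. Treated women who stop early have no described outcome assessment. The planned two-by-two comparison can therefore set treatment completers against controls seen at a somewhat different time.

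The adherence trigger is the main defect. Its likely direction favours CBT, provided early stoppers benefit less than completers. Its size cannot be established from the article: the 0.40 SD and 0.45 SD illustrations against 0.50 SD assume 20% stopping in the treated group, no benefit or half benefit in stoppers, and no selective loss from the wait-list. The timing difference is smaller and may be zero. The conclusion does not depend on how dropouts will be analysed, and it does not show that the plan intends to exclude anyone.

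**What to change.** Reword the assessment sentence in the intervention section, and bring Study Design and Telephone Screening and Study Visits into line, along these lines: *Every enrolled participant will be asked to complete the outcome battery in a single window counted from baseline, whether or not she has attended all four sessions. Participants on the wait-list will complete it in the same window and before their first session.* State the window in days. Analyse women by their initial condition and report the completer analysis as secondary.

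The investigators need to choose a window compatible with the wait that the article describes. The wait-list reassessment must come before treatment, so a window running well past week 4 could conflict with the stated waiting period. They should also reconcile the four weekly sessions with the four weeks of treatment, since the two descriptions place the end of treatment a week apart.

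The cost is small. Virtual visits, REDCap and a $20 gift card per assessment visit are already in place. At the planned 20% attrition about 16 women are concerned (0.20 × 82 = 16.4), or roughly $320 in cards (16 × $20), plus staff time for reminders. Women who withdraw consent will still be missing. If sessions slip, a few treated women will be assessed before, or very shortly after, their last session; that is the price of a common clock, and the secondary completer analysis will show its influence.

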### Data Management

Data collected in this study will be recorded both on paper copies (e.g., informed consent form), as well as electronically stored and managed with Research Electronic Data Capture [REDCap; (45)]. REDCap is a secure, meta-driven web-application used to build online databases, developed with the support from the National Center for Research Resources (NCRR) and the National Institutes of Health (NIH). REDCap follows strict regulatory compliance with standards including the Health Insurance Portability and Accountability Act (HIPAA) and the Federal Information Security Management Act (FISMA), in addition to other international standards. Only the informed consent forms will contain the participant's full name, and the consent forms will be stored separately from all other participant documents. After obtaining informed consent, participants will be assigned with a de-identifying code, and only this code will be recorded on study documents. Additionally, the password protected list indicating the codes and participant names will be stored separately from all other study documents to ensure participant confidentiality.

### Statistical Analysis Plan

Treatment response will be determined using multiple measures, as identified in the assessment battery, and distinguished between primary and secondary efficacy analyses. A series of repeated measures analysis of covariance (ANCOVA) will be used to examine condition differences. A two (treatment vs. wait-list) by two (time: pre-treatment, post-treatment) repeated measures ANCOVA will be used to examine differences in both primary and secondary outcomes, specifically sexual satisfaction and desire, body image, partner satisfaction, vasomotor symptoms, as well as depression and anxiety symptoms. Covariates for all analyses will include age, current marital status, medication use at baseline, treatment delivery method, and baseline depression and anxiety severity. If continuous variables do not meet the assumptions of normality, as assessed by the Shapiro-Wilk test, we will use non-parametric methods, with alpha levels set at 0.05.

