### Study Measures

The assessment battery includes various measures of sexual concerns, vasomotor symptoms, mood, anxiety, relationship, health, body image, cognitive flexibility, and treatment satisfaction. The primary outcome of this trial, sexual satisfaction, is assessed with the Female Sexual Desire Questionnaire. Please see Table 1 for a list of measures and their associated timing.

**Table 1 T1:** Timing of measurements.

**Procedures and Measures**	**CBT-SC-PERI**		**Waitlist** **+** **CBT-SC-PERI**		
	**Baseline**	**Post-treatment**	**Baseline**	**Post-waitlist**	**Post-treatment**

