#### The Hamilton Anxiety Scale

The Hamilton Anxiety Scale (HAM-A) (34) is a clinician administered questionnaire developed to quantify the severity of anxiety symptomatology across 14 items assessing psychic (i.e., mental agitation, distress) and somatic (i.e., physical complaints) anxiety. The HAM-A has demonstrated good validity and reliability in both anxiety and depression populations and is considered a gold-standard (35).

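### The 2 by 2 time factor gives the untreated post-waitlist assessment no stated place, so by the article's own visit labels both groups receive CBT between the two time points

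*Protocol article*

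**What the plan says.** The Statistical Analysis Plan section gives the purpose of the models: "A series of repeated measures analysis of covariance (ANCOVA) will be used to examine condition differences". It then fixes the factors, for the primary and the secondary outcomes alike: "A two (treatment vs. wait-list) by two (time: pre-treatment, post-treatment) repeated measures ANCOVA will be used". Post-waitlist does not appear anywhere in that section.

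Study Design describes what happens to women who have to wait: "They will then be re-assessed after the 4-week waitlist period and then undergo the four-session treatment, followed by a post-treatment assessment". The column labels of Table 1 match this, with two assessments for immediate treatment followed by three for the wait-list group: "Baseline Post-treatment Baseline Post-waitlist Post-treatment". The section on telephone screening and study visits has wait-listed women "complete the self-report measures following the waitlist period/before starting treatment". The section describing the CBT programme places the post-treatment assessment within two weeks after the four sessions, with no separate definition for wait-listed women.

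**The concern.** The wait-list group acts as a control only between baseline and post-waitlist. The model needs that interval in order to compare CBT with no CBT. As labelled, its second time level is post-treatment, which for wait-listed women is a post-CBT value. Post-waitlist comes before treatment starts, so by its description it fits the pre-treatment level at least as well as the follow-up level.

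The main efficacy contrast is at stake, because this one sentence governs the primary and the secondary outcomes. An analyst who follows the labels would compare two treated groups. If the mapping of visits to time levels stays open, it could also be settled after the data have been seen.

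**Working it through.** **Inputs.** From Sample Size: effect size 0.5, alpha 0.05, power 80%, 68 participants required. From Study Design and Table 1: the assessment sequence in each group. Assumptions, because the article does not state them: a two-sided test, equal groups (34 per arm), and 0.5 read as a standardised mean difference.

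**The plan's own figure.** Without adjustment, n per arm = 2(1.960 + 0.842)²/0.5² = 62.8, so 63 per arm and 126 in total. ANCOVA multiplies this by (1 − ρ²). To reach 34 per arm, ρ = √(1 − 34/62.8) ≈ 0.68, a correlation that the article does not give. The 68 therefore does not follow from the stated inputs alone. The present point does not depend on it: below, precision is set so that a contrast of 0.5 has exactly the planned 80% power.

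**What each reading estimates.** Let T_I and T_W be the change across the CBT period in the immediate and wait-list groups, and W the wait-list group's change over the wait that persists to its final visit.

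| Wait-list time points | Group-by-time contrast |
|---|---|
| A. Post-waitlist to post-treatment | T_I − T_W |
| B. Baseline to post-treatment | T_I − (W + T_W) = (T_I − T_W) − W |
| C. Baseline to post-waitlist | T_I − W |

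A and B both fit the labels, because baseline and post-waitlist both precede treatment. In each, CBT lies inside both windows and its effect cancels when response is equal. Only C sets CBT against no CBT, and C needs post-waitlist as the second time level.

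**Size.** Calibrated residual SD = √(34/62.8) = 0.736. SE of the contrast = 0.736 × √(2/34) = 0.1785. The two-sided rejection probability for a contrast of size δ is Φ(δ/SE − 1.96) + Φ(−δ/SE − 1.96).

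| Reading | Size of contrast | Rejection probability |
|---|---|---|
| C, with T_I = 0.5 and W = 0 | 0.5 | 80% |
| A with T_I = T_W, or B with T_I = T_W and W = 0 | 0 | 5% |
| B, T_I = T_W, W = 0.1 | 0.1 | 8.7% |
| B, T_I = T_W, W = 0.2 | 0.2 | 20% |
| B, T_I = T_W, W = 0.25 | 0.25 | 29% |

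In the last three rows a significant result would show change over the wait. The CBT effect does not enter the contrast.

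**The case against.** The best defence is that the wording is loose and the design is sound. The factor is called treatment versus wait-list, the stated aim is to compare conditions, and a wait-list condition exists only up to post-waitlist. Collecting the outcome battery at that visit makes little sense unless it serves as the untreated follow-up. The pre-treatment label does not appear in Table 1, so the text does not settle which visit it means. The article is also condensed, and a full analysis plan may map time levels to visits.

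Most of this stands as an account of intent: baseline to post-waitlist is probably what the authors had in mind. It does not remove the point. The article states the time levels outright, so this is not a detail left for another document, and Table 1 uses post-treatment for the wait-list group's visit after CBT.

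Two stronger readings are tempting, and the documents do not support them.

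- A reader might infer that the contrast is zero however well CBT works, or that the trial cannot answer its question. The zero needs equal response in both groups, which is not assured when allocation follows clinician availability. On reading B it also needs no change over the wait. The untreated follow-up is scheduled, so the right comparison remains available.
- A reader might infer that anxiety has no control value, because the Hamilton Anxiety Scale "is a clinician administered questionnaire" while the visit section mentions only self-report measures at post-waitlist. But Table 1 schedules the scale at that visit, and the Abstract lists anxiety among the outcomes assessed there. The visit section also describes baseline as diagnostic interviews plus self-report measures, although Table 1 schedules the scale at baseline too. The phrase is shorthand for the outcome battery.

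**Conclusion.** The point holds as a mis-specified time factor in the stated efficacy model. By the article's own labels, CBT falls between the two time points in both groups, and the contrast does not estimate CBT versus no CBT. With equal response and no change over the wait, the rejection rate is 5% instead of 80%. Without those conditions, the contrast picks up a difference in response or, on the baseline reading, change over the wait as well. The percentages rest on 34 per arm, a two-sided test and precision calibrated to the planned power. The structural conclusion needs none of these. It concerns the written rule: the authors may have intended the right comparison, and the visits needed for it are in the schedule.

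**What to change.** In the Statistical Analysis Plan section, replace the two time labels with named assessments: baseline versus end of the first period, where the end of the first period is post-treatment for the immediate group and post-waitlist for the wait-list group. State that the wait-list group's later post-treatment data do not enter this contrast. They can be used in a separate within-person analysis that compares change over the wait with change over CBT in the same women.

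The cost is a few sentences of text, with no new visit, measure or participant. The change should be made before outcome data are examined, so that the choice of wait-list time points cannot depend on results. It does not address the comparability of groups formed by clinician availability, which is a separate matter.

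### The planned 2x2 pre/post model leaves the primary outcome's own baseline, and that of most secondary outcomes, off the covariate list and so gives up some power that the collected data could supply

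*Protocol article*

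**What the plan says.** The Statistical Analysis Plan section states: "A series of repeated measures analysis of covariance (ANCOVA) will be used to examine condition differences". It then fixes the layout: "A two (treatment vs. wait-list) by two (time: pre-treatment, post-treatment) repeated measures ANCOVA will be used to examine differences in both primary and secondary outcomes". The pre-treatment score is therefore one of the two responses in the model. The covariates are fixed as well: "Covariates for all analyses will include age, current marital status, medication use at baseline, treatment delivery method, and baseline depression and anxiety severity". The list includes the starting level of two outcomes, depression and anxiety. It does not include the starting level of the primary outcome, sexual desire, body image, partner satisfaction or vasomotor symptoms. Table 1 schedules every outcome measure it lists at baseline, post-treatment and, for the waitlist group, post-waitlist.

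The article names the Female Sexual Desire Questionnaire as the primary measure under Study Measures, and the Female Sexual Function Index in Table 1 and under Primary Outcome. Neither instrument's baseline is a covariate, so the point is the same on either reading.

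The Sample Size section says "we estimate a medium effect size of 0.5 for our study" and "Using an ANCOVA power analysis to calculate sample size", and concludes with "a study power set at 80%, 68 participants are required to conduct our study". It names no covariate, pre-post correlation or sidedness.

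**The concern.** In a model with one pre and one post measurement, the condition-by-time interaction is arithmetically a comparison of mean change between the groups. Subtracting the full baseline fixes its coefficient at 1. An ANCOVA of the follow-up score estimates that coefficient from the data, which leaves less residual variance whenever the true slope is not 1. The baseline is thus used in the planned model, but not in the most efficient way.

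Two things are at stake. One is power on the primary outcome, from data that will be collected anyway. The other is consistency: depression and anxiety, whose baselines are covariates, may in effect be baseline-adjusted, while the primary outcome gets a plain change score. The article gives no reason for treating the primary outcome less efficiently.

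**Working it through.** **Inputs.** From the Sample Size section: effect size 0.5, α = 0.05, power 80%, 68 evaluable participants. Assumed, because the article does not state them: 0.5 is a standardised mean difference, the test is two-sided, the groups are equal (34 each), pre and post variances are equal, and r ranges from 0.5 to 0.8.

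**The plan's own figure.** Without any baseline information, N = 4(1.960 + 0.842)²/0.5² = 125.6, so 126 in total (128 with the t distribution). The figure of 68 therefore does not follow from the stated inputs alone. It can be reached in more than one way:

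- ANCOVA with own baseline: 126(1 − r²) = 68 gives r = √(1 − 68/126) ≈ 0.68.
- 2x2 interaction (change score): 126 × 2(1 − r) = 68 gives r = 1 − 68/252 ≈ 0.73.
- Twice the 34 needed for a paired test at 0.5 is also 68.

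The article does not allow a choice among these.

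**Variance of each estimator**, relative to a comparison of follow-up scores alone:

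- ANCOVA on own baseline: 1 − r²
- Change score: 2(1 − r)
- Ratio: 2(1 − r)/[(1 − r)(1 + r)] = 2/(1 + r), which exceeds 1 for every r below 1.

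**Power at 34 per group, d = 0.5** (non-central t; the noncentrality is 0.5√(34/2) divided by the square root of the variance factor; one degree of freedom is taken off for the baseline covariate):

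| Assumed r | 1 − r² | 2(1 − r) | Ratio | ANCOVA | Change |
|---|---|---|---|---|---|
| 0.5 | 0.75 | 1.00 | 1.33 | 65% | 53% |
| 0.6 | 0.64 | 0.80 | 1.25 | 72% | 62% |
| 0.68 | 0.54 | 0.64 | 1.19 | 79% | 72% |
| 0.7 | 0.51 | 0.60 | 1.18 | 81% | 75% |
| 0.8 | 0.36 | 0.40 | 1.11 | 92% | 90% |

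Simulation at 34 per group agrees: 64% vs 53% at r = 0.5 and 79% vs 72% at r = 0.68.

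**In participants** (normal approximation, rounded up per group), the evaluable totals for 80% power, ANCOVA vs change, are 96 vs 126 at r = 0.5, 68 vs 82 at r = 0.68 and 46 vs 52 at r = 0.8.

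**Depression and anxiety.** Suppose the covariates act on the time contrast and the listed severity scores are the outcome measures themselves. The model for change is then y₁ − y₀ = a + b·condition + c·y₀, which rearranges to y₁ = a + b·condition + (1 + c)·y₀. The condition coefficient b is the one from a follow-up ANCOVA. Under those two conditions these outcomes already get the more efficient estimator and the primary outcome does not.

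**Not in these figures.** The other listed covariates would absorb some variance under either model, by an amount the article does not allow to be computed. The entry cut-off on the Female Sexual Function Index may also shrink the baseline SD. With unequal SDs s₀ and s₁, the change-score variance exceeds the ANCOVA variance by (s₀ − r·s₁)². That is never negative, but it becomes smaller as s₀ falls towards r·s₁.

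**The case against.** The strongest reply has three parts.

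*The change contrast is a valid and common analysis, and the loss may be small.* This stands. At r = 0.8 the gap is about 3 percentage points, and at higher r it is negligible. It is a matter of efficiency and not an error that invalidates the result.

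*Allocation is not randomised.* Under Study Design, women wait when no clinician is immediately available. If the groups differ at baseline, a change score and a baseline-adjusted comparison can estimate different effects, so the choice concerns bias as well as power. This stands as a caveat. It is not a reason to prefer the change score, which needs its own assumption that both groups would have changed equally without treatment. The described mechanism turns on clinician availability and not on the participant's score, which favours adjustment, although the article does not state that the two are unrelated.

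*The sizing may have used the planned model.* This also stands. A reader might infer that 68 came from a baseline-adjusted ANCOVA and that the analysis therefore contradicts it. The article does not say which ANCOVA was meant, and the 2x2 interaction gives the same total at r of about 0.73.

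A reader might also take condition differences to mean the group effect averaged over both times, which would have only about 20% power. The natural test of a condition-by-time layout is the interaction, and nothing in the article says that the averaged effect will be tested.

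**Conclusion.** The point holds as a matter of efficiency. The covariate list leaves out the own baseline of the primary outcome and of the secondary outcomes other than depression and anxiety, and the condition-by-time test is then a change-score comparison. At 34 per group and d = 0.5 the cost is about 12 percentage points of power at r = 0.5, 7 at r = 0.68 and 3 at r = 0.8. These figures rest on an assumed r, equal groups, equal variances and a two-sided test.

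It would be too strong to say that every outcome's baseline is missing, since two are listed, or that baseline is ignored, since it is the first level of the time factor. A contradiction between sizing and analysis is not demonstrated. What is certain about the sizing is that 68 depends on something the article does not state.

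**What to change.** Replace the 2x2 model with an ANCOVA for each outcome. The response is the end-of-first-period score: post-treatment in the immediate group, post-waitlist in the waitlist group. The terms are condition, the baseline value of the same outcome and the covariates already listed. Where baseline depression or anxiety is the outcome's own baseline, enter it once. Report the adjusted mean difference with its 95% CI. The own baseline should not simply be added to the existing 2x2 model, where it is already a response.

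Because allocation follows clinician availability, tabulate the two groups at baseline and give the change-score result as a sensitivity analysis. State in the Sample Size section which model and which pre-post correlation gave 68.

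The cost is one degree of freedom per model, revised wording and a little more analysis work. No new data are needed.
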